## Abstract:

**Background:** The purpose of this study is to describe disease trends, outcomes, and risk factors for pediatric tuberculosis infection in rural vs urban settings.

**Methods:** To determine disease trends in the number of diagnosed pediatric tuberculosis cases in rural vs urban settings, in Aim 1, we will complete a retrospective study of 100 children, <15 years old, diagnosed with active tuberculosis from January 2016-June 2021 at Mulago National Referral Hospital and Fort Portal Regional Referral Hospital. We hypothesize that the number of diagnosed tuberculosis cases in both rural and urban settings will decrease over time. Using this same population, in Aim 2, we will complete a historic cohort study to determine pediatric tuberculosis outcomes in rural vs urban settings. We hypothesize that length of hospital stay is longer, and mortality is higher among children with tuberculosis in rural compared to the urban hospital settings. Medical records will be reviewed using a standardized chart abstraction protocol. To identify possible risk factors for development tuberculosis infection in children, in Aim 3, we will perform a cross-sectional descriptive study of children with active tuberculosis, obtaining a risk-factor history via a questionnaire at an outpatient tuberculosis clinic.

**Study Utility:** These results will improve our understanding of rural healthcare disparities in Uganda and provide preliminary data for larger studies to address tuberculosis risk factors and predictors of poor tuberculosis treatment outcomes among children.

[figure not shown]

**Background:**

According to the World Health Organization Global Tuberculosis Report, children <15 years accounted for 12% of the 10 million tuberculosis (TB) cases and 192,000 total deaths in 2019 (1). Estimating the global burden of TB in children is difficult as many cases are undiagnosed due to the frequency of extra-pulmonary TB, non-specific symptoms, the paucibacillary nature of pediatric TB, and lower public health priority (2,3).

Uganda has a high burden of TB infection with an incidence rate of 200 per 100,000 individuals. Children <15 years account for 12% of all cases (6). In 2015, through a revised National Strategic Plan, the Uganda National Tuberculosis and Leprosy Program emphasized the importance of recognizing tuberculosis in children, including increasing the capacity of health workers to screen and diagnose childhood and extra-pulmonary TB (7).

The burden of TB disease is generally considered to be higher in urban compared to rural settings due to factors like overcrowding and higher prevalence of HIV infection (8,9,10). However, urban settings are also associated with greater healthcare delivery and improved access to healthcare providers and facilities (11). Prior observational studies have looked at pediatric TB trends and outcomes in Kampala district (12,13). However, additional research is needed to understand disease trends and outcomes in rural settings.

**Objectives:**

The primary objectives are:

1. To describe the trends of paediatric TB cases identified over a 5-year period among children <15 years of age in rural and urban settings.
2. To describe the TB treatment outcomes among children < 15 years of age admitted with TB disease in rural and urban settings.
3. To identify risk factors that are present in children <15 years of age with active TB in rural and urban settings.

Specific Hypotheses to be Tested:

[figure not shown]

1. The number of diagnosed TB cases initiating therapy in rural and urban settings will decrease over time.
2. Length of hospital stay in days (LOS) for children with TB is longer in the rural setting vs the urban setting.
3. Mortality is higher among children with TB in the rural hospital setting vs the urban hospital setting.

## **METHODS**

### **Study design**

Aims 1 and 2 are a retrospective study and historic cohort study design, respectively, collecting data on all forms of TB in the period of January 1, 2016 to June 30, 2021. Aim 3 is a descriptive cross-sectional study using a survey given to children with active TB, currently receiving treatment at an outpatient tuberculosis clinic.

### **Study setting**

The study will be implemented at Mulago National Referral Hospital and Baylor College of Medicine Children's Foundation Uganda (Baylor-Uganda) as the urban setting, and Fort Portal Regional referral hospital as the rural setting.

Mulago National Referral Hospital is a public health facility that admits children with severe disease through the acute care unit (paediatric emergency unit) to the paediatric inpatient wards until discharge. The facility provides tertiary health care and TB diagnostic and treatment services. Children with pulmonary tuberculosis are admitted to the paediatric pulmonology-cardiology ward and children with TB meningitis are admitted to the paediatric neurology ward which are adjacent to each other. Children admitted with all forms of TB that require follow-up after discharge are discharged through the paediatric TB out-patients clinic within Mulago Hospital. Records about HIV treatment for HIV-infected children will be obtained from medical records at the HIV care clinic.

Fort Portal regional referral hospital is a regional hospital that services the entire South-Western region in Rwenzori. The facility provides tertiary health care and TB diagnostic

and treatment services. All patient records are stored and managed by the hospital records departments.

### **Study Procedures:**

#### Retrospective study and historic cohort study

We will perform a retrospective chart review of electronic and written medical records for 100 children <15 years of age who were diagnosed with TB at either Mulago National Referral Hospital or a Fort Portal Regional Referral Hospital in Uganda. Cases will be included between January 1, 2016 - June 30, 2021. The medical records will be reviewed, and eligibility will be confirmed through the inclusion and exclusion criteria. If the patient is eligible, the abstractor will proceed with a standardized chart abstraction form. If the patient is not eligible, the abstractor will look for an alternative case until the 100-patient sample is reached. Data elements to be extracted include: name, medical record number, date of birth, sex, address, nationality, ethnicity, hospital admission and discharge date, weight, height, diagnosis at admission, clinical symptoms at admission, date of symptoms onset, history of prematurity, birth weight, prior medical problems, BCG vaccination, history of TB contacts, prior history of TB infection, HIV infection status, CD4 count/percentage and viral load in HIV-infected, TB diagnostics (AFB, culture, PPD), radiographic imaging reports, biopsy reports, cerebral spinal fluid labs, major procedures or interventions, TB treatment regimen, treatment adverse reactions, anti-retroviral treatment regimen for HIV-infected, final diagnosis, discharge status, and follow-up recommendations. When available, data from the 12-month follow-up visit will also be abstracted.

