#### **Exclusion criteria:**

##### Retrospective study and historic cohort study

1. Age greater than or equal to 15 years
2. The patient was determined not to have TB during the admission
3. Clinical notes irretrievable
4. Meningitis in post-operative setting, post-traumatic meningitis, or parameningeal infections
5. Chronic meningitis other than tuberculous meningitis

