### **Study Statistics:**

#### Retrospective study and historic cohort study

The primary outcome variables are TB active case trends and treatment outcome at the time of hospital discharge. We will assess all available charts of pediatric patients admitted with active TB. Means and standard deviations (SD) for continuous variables, frequency and percentage for categorical variables will be used to summarize all predictor variables and the outcome variables. Comparisons of categorical variables will be made using Chi-square and comparison of continuous variables will be completed using independent t-tests or nonparametric tests depending on normality of distribution.

To test Hypothesis 1, that the number of diagnosed TB cases initiating therapy in rural and urban settings will decrease over time, we will fit a linear regression model with number of monthly cases diagnosed as outcome and study period (in months) as the predictor with the initial month of the study period (01-Jan-2016) represented as "1" and the final month of study period 06-Jun-2021 represented as "66", accepting a linear assumption that cases are evenly distributed across each month. We will further fit an interaction term in this regression model, between dichotomous TB diagnosis location (urban or rural) and continuous study period. In an alternative model, we will test for the bivariate correlation between the annual number of cases diagnosed and the year of diagnosis by computing the Pearson's correlation coefficient, with significant temporal trend defined as a  $p < 0.05$ . To test Hypothesis 2, that length of hospital stay in days (LOS) for children with TBM is longer in rural vs urban settings, we will fit a linear regression model with LOS as continuous outcome and location as dichotomous predictor, controlling for a-prior selected potential confounders. To test Hypothesis 3, that mortality is higher among children with TBM in the rural hospital setting vs the urban hospital setting, we will fit a multivariable logistic regression model with in-hospital mortality as dichotomous outcome and location as dichotomous predictor.

[figure not shown]

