### **The proposed research plan is to:**

Complete a retrospective case series study of 100 children, <15 years old, diagnosed with active tuberculosis from January 1, 2016- 30th June 2021. Medical records will be reviewed using a standardized chart abstraction protocol.

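### Aim 1 reads a trend in case numbers from a chart sample capped at 100 with no stated selection rule, while the statistics section says all charts are assessed; if more than about 100 cases are eligible, the trend could be distorted

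*Protocol*

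**What the plan says.** The Objectives section states Hypothesis 1: "The number of diagnosed TB cases initiating therapy in rural and urban settings will decrease over time". The Study Statistics section tests it with a linear regression that has the "number of monthly cases diagnosed as outcome and study period (in months) as the predictor", months running from 1 to 66. It adds a location-by-time interaction and, as an alternative, a Pearson correlation of annual counts with year. Case trend is named there as a primary outcome.

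The data source is described in four places:

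- Abstract, on how the Aim 1 trend will be determined: "we will complete a retrospective study of 100 children, <15 years old, diagnosed with active tuberculosis from January 2016-June 2021". It then makes Aim 2 depend on the same children: "Using this same population, in Aim 2, we will complete a historic cohort study".
- Study Procedures, retrospective part: if a chart is ineligible, "the abstractor will look for an alternative case until the 100-patient sample is reached".
- Waiver request, research plan: "Complete a retrospective case series study of 100 children".
- Study Statistics: "We will assess all available charts of pediatric patients admitted with active TB".

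The first three fix the sample at 100; the fourth implies a full count. The size of 100 is derived from length of stay (Hypothesis 2) only. The exclusion criteria for the chart review also remove cases under "Clinical notes irretrievable".

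**The concern.** A case count is informative only if the total is free to vary. Here the total is set in advance by a calculation for another hypothesis. Once more than about 100 cases are eligible, the number falling in each month and hospital depends on which charts are opened, and the protocol does not say how they are chosen. The waiver request allots one month to the project, so choosing charts by convenience is plausible, though nowhere stated.

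At stake is a primary outcome. Working from the oldest chart forward would produce a decline and appear to support Hypothesis 1; working backward would produce a rise. The site-by-time interaction is exposed in the same way if the two hospitals pull charts differently. The exclusion for irretrievable notes adds a second route: if older notes are harder to find, counts rise over time for that reason alone. No later analysis can recover cases that were never counted.

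**Working it through.** **The plan's own figure.** The 100 charts come from a length-of-stay difference of 16 days with more than 80% power. The SD, alpha and allocation are not stated. Assume SD = (60 − 21)/1.349 = 28.9 days, from the quoted IQR, with two-sided alpha 0.05 and 50 charts per hospital. Power is then 79.0% by the normal approximation and 78.2% by the noncentral t. The figure is reproduced approximately, and nothing in it concerns the trend.

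**What the cap does to the counts.** 100 charts over 66 months is 100/66 = 1.5 per month, whatever the true caseload.

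**Hand check of date-order filling.** The true caseload is an assumption, taken as flat. The regression slope is Σ(t − 33.5)y / Σ(t − 33.5)², with Σ(t − 33.5)² = 66 × (66² − 1)/12 = 23,952.5.

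- 5 cases per month (330 eligible), oldest first: 100 charts are reached in 20 months. Numerator: 5 × (210 − 20 × 33.5) = −2,300. Slope: −2,300/23,952.5 = −0.096.
- 2 cases per month (132 eligible), oldest first: 100 charts are reached in 50 months. Numerator: 2 × (1,275 − 50 × 33.5) = −800. Slope: −800/23,952.5 = −0.033.

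Newest-first filling gives the same slopes with the opposite sign.

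**Simulation.** Flat Poisson monthly counts, analysed with the planned regression:

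| True rate per month | Eligible (expected) | Mean slope, date order | p<0.05, date order |
|---|---|---|---|
| 1.7 | about 112 | – | about 42% |
| 2 | 132 | −/+0.03 | about 89% |
| 3 | 198 | −/+0.07 | 100% |
| 5 | 330 | −/+0.10 | 100% |

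A simple random draw of 100 gave a mean slope of about 0 and p<0.05 in about 5% of runs at each of these rates.

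**Milder selection.** With 200 eligible charts, a flat truth, and a retrieval chance that doubles from the start to the end of the period, a false significant rise appears in 28% of runs.

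**When cases truly halve over the period (200 eligible).**

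- Full count: decline found in 77% of runs.
- Random 100: decline found in 50%.
- Newest first: a significant rise in 100%.
- Quotas spread evenly over the years, with about half a quota for the half-year 2021: decline found in 0%.

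**What a random 100 cannot show.** For the same halving, the mean slope of a full count is −0.031, −0.062 and −0.124 with 200, 400 and 800 eligible charts. The mean slope of a random 100 is −0.016, −0.016 and −0.015. The absolute size of the decline is lost.

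**The case against.** **No passage says charts are pulled in date order, and the number of eligible charts is not given.** This stands. A reader might infer that the trend will reflect chart order rather than diagnoses; the protocol supports only that it could, because selection is left open.

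**The Study Statistics section can be read as a full count.** It can, but the Abstract, Study Procedures and waiver request all say 100, and an abstractor following the procedures stops there. The sentence is one half of a contradiction and does not settle it.

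**A random draw would be unbiased for direction.** Correct. One might conclude that distortion is avoided only if 100 or fewer cases are eligible; the random-draw results show that this is too strong. But the protocol specifies no such draw, and it would still cost power and the absolute counts.

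**The effect is not overwhelming at every caseload.** Also correct. At 2 cases per month only about 59% of date-order runs reach p<0.001, and near 112 eligible cases only about 42% reach p<0.05.

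**Equal yearly quotas need not give a flat line.** The window holds six months of 2021. Equal calendar-year quotas of 100/6 = 16.7 put 1.39 cases in each month up to month 60 and 2.78 in each of the last six. The slope is 1.39 × (381 − 6 × 33.5)/23,952.5 = +0.010 per month.

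**A monthly count needs more than a date and a site.** True under this protocol: age under 15, start of therapy and not later being found free of TB must each be confirmed. Simply ignoring the irretrievable-notes exclusion would admit cases whose eligibility is unknown.

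**Conclusion.** The concern holds in conditional form. The protocol contradicts itself on whether Aim 1 uses 100 charts or all charts, and it gives no rule for choosing the 100. If more than about 100 cases are eligible, absolute caseload and the urban-rural difference in level cannot be estimated, and selection that is not random in time can create, hide or reverse a trend. Under a flat caseload, the false slope from date-order filling is about 0.03 cases per month at 2 cases per month and 0.10 at 5 per month. These sizes rest on assumed caseloads, Poisson counts and strict date-order filling; weaker time-dependence does less harm.

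The documents do not show that the trend is certain to be an artefact. If about 100 cases or fewer are eligible in total, or if the draw is random, the expected direction survives. The point should still be settled before abstraction, because the rule as written can leave a primary outcome uninterpretable.

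**What to change.** 1. **Aim 1:** count every child under 15 diagnosed with TB and starting therapy, per month and per hospital, January 2016 to June 2021, without the 100 cap. Use the EMR query, TB registers or records-department lists. Confirm age, treatment start and not-TB status from those sources. Report the number of cases with irretrievable notes by period and site, so that they are not dropped silently.
2. **Aim 2:** keep the 100-chart sample for this aim only. Draw it in random order from the Aim 1 list, replace an ineligible chart with the next on the list, and state the site split.
3. **Wording:** reconcile the Abstract, Study Procedures, Study Statistics and the research plan in the waiver request. The waiver now describes 100 children and would have to cover the wider count.
4. **Fallback:** check that the lists are complete at both hospitals. If a full list cannot be obtained, limit Hypothesis 1 to a relative trend from a random sample and say so.

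The cost is a modest extra tally at both hospitals. The Budget already includes an EMR interrogation fee and a records assistant at each site, which covers part of it. It is not free: records are partly on paper, the protocol does not say that complete lists exist, and only one month is allotted.

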#### Descriptive cross-sectional study

We will also perform a descriptive cross-sectional study using standard questionnaire to identify possible risk factors for TB development. This questionnaire will be administered to a total of 50 children; 25 children (<15 years of age) with any form of TB disease at outpatient clinics at Mulago National Referral Hospital and 25 children (<15 years of age) with any form of TB infection at outpatient clinics at Fort Portal referral hospital. Data

collected from the questionnaire includes length of time between symptom onset and treatment initiation, nutrition status, HIV infection, BCG status, overcrowding, exposure to indoor and outdoor air pollutants, and indirect markers of poverty. We will then look at the subject's medical record to collect information about their disease status including hospital admission date, weight, height, diagnosis codes, clinical symptoms, prematurity, birth weight, prior medical problems, TB diagnostics, radiographic imaging reports, biopsy reports, treatment regimen, culture results, and major procedures or interventions.

#### **Inclusion criteria:**

##### Retrospective study and historic cohort study

1. Patients presenting to Mulago National Referral Hospital or Fort Portal Regional Referral Hospital between 01-Jan-2016 to 30-June-2021
2. Males and females 0 to <15 years
3. Presumptive pulmonary or extra-pulmonary TB cases based on clinical symptoms and/or positive AFB smear, culture, or molecular-confirmed disease

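### The chart-review criteria accept presumptive TB on symptoms alone, contradicting the diagnosed, treated or active TB population stated elsewhere; this dilutes the rural-urban contrasts and can bias them in an unknown direction

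*Protocol*

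**What the plan says.** **The eligibility rule.** Under Inclusion criteria, the third criterion for the retrospective and historic cohort study is "Presumptive pulmonary or extra-pulmonary TB cases based on clinical symptoms and/or positive AFB smear, culture, or molecular-confirmed disease". Under Exclusion criteria, the second item is "The patient was determined not to have TB during the admission". The remaining exclusions that turn on a diagnosis concern meningitis only, for example "Chronic meningitis other than tuberculous meningitis". Study Procedures makes these lists decisive: "eligibility will be confirmed through the inclusion and exclusion criteria".

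**The population described elsewhere.**
- The Abstract speaks of children "diagnosed with active tuberculosis from January 2016-June 2021", and the research plan in the waiver request says the same in substance.
- Hypothesis 1 under Objectives reads "The number of diagnosed TB cases initiating therapy in rural and urban settings will decrease over time".
- Study Procedures opens the chart review with children "who were diagnosed with TB at either Mulago National Referral Hospital or a Fort Portal Regional Referral Hospital in Uganda".
- Study Statistics states "We will assess all available charts of pediatric patients admitted with active TB".

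**The concern.** The written test for entry is wider than the population that the hypotheses address. A child suspected of TB on symptoms, with no recorded diagnosis and no treatment, satisfies the third inclusion criterion. That child is removed only if someone at the hospital concluded that TB was absent. A child who was not worked up, or whose work-up was inconclusive, meets the criteria.

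Two consequences follow. First, the conflict leaves the abstractors to choose between the criteria and the narrower descriptions, and staff at the two hospitals could choose differently. Second, an exclusion that needs an active rule-out depends on how much each hospital investigates. Hospital setting is the predictor in Hypotheses 2 and 3, and calendar time is the predictor in Hypothesis 1. If work-up differs by hospital or changes over the study period, the share of non-TB children differs along the axis being analysed.

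**Working it through.** **1. The passages side by side**

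| Place in protocol | Population |
|---|---|
| Inclusion criterion 3 | presumptive; symptoms alone suffice |
| Exclusion criterion 2 | removed only after an active rule-out |
| Abstract; waiver request | diagnosed, active TB |
| Objectives, Hypothesis 1 | diagnosed and starting treatment |
| Study Procedures | diagnosed at either hospital |
| Study Statistics | admitted with active TB |

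The first two rows are operative, because Study Procedures confirms eligibility through them. Neither mentions a recorded diagnosis or started treatment. The cross-sectional study uses the same presumptive wording but also requires that the child is receiving outpatient TB treatment. The chart review has no such condition.

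**2. The plan's own figure.** Study Statistics claims more than 80% power with n = 100 for a difference in length of stay above 16 days, citing an interquartile range of 21-60 days. Assumptions: 50 charts per hospital, two-sided 5% level, normal approximation.
- SD = (60 - 21)/1.349 = 28.9 days.
- SE = 28.9 × √(2/50) = 5.78 days.
- Power = Φ(16/5.78 - 1.96) = 79.0% (78.2% with the noncentral t).

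The stated figure is essentially reproduced and serves as the baseline.

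**3. Effect of admitting non-TB children (illustration).** Let f_U and f_R be the non-TB shares at the urban and rural hospital. Let D be the number of days by which a non-TB stay is shorter than an urban TB stay, taken as equal at both hospitals. Let Δ be the true rural-minus-urban difference among TB cases. Then

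observed difference = (1 - f_R)·Δ - f_R·D + f_U·D.

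The shares and D are assumptions; the documents give neither. The SD is held at 28.9 days. Power counts significance in the rural-longer direction.

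| f_U / f_R | D | Observed if Δ = 0 | Rejection rate | Observed if Δ = 16 | Power |
|---|---|---|---|---|---|
| 0 / 0 | any | 0 | 5% | 16.0 | 79% |
| 20% / 20% | 10 to 30 | 0 | 5% | 12.8 | 60% |
| 10% / 20% | 10 | -1.0 | 5.3% | 11.8 | 53% |
| 10% / 30% | 20 | -4.0 | 10.6% | 7.2 | 24% |
| 10% / 40% | 30 | -9.0 | 34.4% | 0.6 | 3% |
| 30% / 10% | 20 | +4.0 | 10.6% | 18.4 | 89% |

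For example, the fourth row gives 0.7 × 16 - 0.3 × 20 + 0.1 × 20 = 7.2 days.

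Equal shares leave a true zero at zero but shrink a true difference. Unequal shares shift the contrast, and the sign follows whichever hospital has more non-TB children.

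**4. Mortality (illustration).** Assume 10% deaths in TB cases at both hospitals and non-TB shares of 10% urban and 30% rural.
- Non-TB mortality 3%: urban 0.9 × 10% + 0.1 × 3% = 9.3%; rural 0.7 × 10% + 0.3 × 3% = 7.9%. The odds ratio is (0.079/0.921)/(0.093/0.907) = 0.84.
- Non-TB mortality 20%: urban 11%, rural 13%. The odds ratio is (0.13/0.87)/(0.11/0.89) = 1.21.

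A true odds ratio of 1 can therefore move either way.

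**The case against.** **The narrower wording may govern.** Study Procedures starts from children already diagnosed with TB and applies the criteria to those charts, so an undiagnosed child might never be reached. This has weight, and it means enrolment of such children is possible rather than certain. It does not remove the conflict. An exclusion for children found not to have TB would have little purpose if every screened chart carried a settled diagnosis, and the criteria are named as the test of eligibility.

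**A reader might infer that the rural-urban comparison is biased, with the rural hospital keeping more non-TB children.** The documents do not support that. Study setting describes diagnostic and treatment services at both hospitals in the same terms. Background says only in general that urban settings have better access to care. There are no work-up rates and no stay or mortality figures for non-TB children.

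**A reader might also infer that better diagnostics over time would produce a spurious fall in cases.** Background describes a 2015 national plan to strengthen screening and diagnosis of childhood TB, which could equally raise the count.

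**Clinical diagnosis is legitimate.** Background notes how few bacilli children with TB carry, so accepting cases without bacteriological proof is reasonable. This stands in full. The fault is accepting suspicion without any recorded diagnosis or treatment.

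**A stricter definition has its own problems.** A recorded diagnosis also depends on work-up, and requiring one can drop true TB cases who died early, which selects on the outcome of Hypothesis 3. Adjusting for confirmation status would adjust for something that may itself follow from hospital setting. These points stand and shape the fix.

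**Sensitivity analyses may be in a SAP that is not shown.** Their absence is not counted here. Eligibility, however, is fixed in the protocol and decides which 100 charts are abstracted.

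**Conclusion.** The point holds as an internal contradiction with statistical consequences. The eligibility criteria can admit children with no recorded TB diagnosis and no TB treatment, while the hypotheses and population descriptions concern diagnosed, treated or active TB. Admitting non-TB children dilutes a true rural-urban difference, and can bias the contrast if their share differs by hospital or over time.

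The direction is unknown and the size cannot be read from the documents. Over the assumed range with more non-TB children at the rural hospital (10% urban, 20-40% rural, stays 10-30 days shorter), a true zero appears as -1 to -9 days and a true 16 days as 11.8 to 0.6 days. Reversing the shares reverses the sign of the null shift. These figures show that the case definition can matter against a 16-day target. They do not estimate what will happen at these hospitals.

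**What to change.** - Reword inclusion criterion 3 to require a TB diagnosis recorded by the treating team, clinical or bacteriological, or started anti-TB treatment. Apply it identically at both hospitals, and make the population descriptions elsewhere agree with it.
- For Hypothesis 1, count only children with anti-TB treatment started, as the hypothesis itself states.
- Keep clinically diagnosed cases.
- For Hypothesis 3, flag presumptive cases who died before a diagnosis was settled, and repeat the analysis with them included, so that the definition does not select on death.
- Report bacteriologically confirmed versus clinically diagnosed status by hospital, but do not adjust the main models for it.

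The cost is small. Final diagnosis, TB diagnostics, treatment regimen and discharge status are already among the data elements in Study Procedures. Some presumptive charts would be replaced under the existing rule for finding alternative cases, and deaths before a settled diagnosis would have to be abstracted for the repeat analysis. The new definition does not wholly remove dependence on each hospital's work-up, which is why case status should be shown by site.
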